
#### Mortality at 1 year

Date of death will be obtained via the National Medical Information Service.

### Secondary outcomes

#### Physical fitness ($$ \overset{.}{\mathrm{V}}{\mathrm{o}}_2 $$ peak) and preoperative risk categories derived from CPET

CPET derived $$ \overset{.}{\mathrm{V}}{\mathrm{o}}_2 $$ at $$ {\widehat{\uptheta}}_{\mathrm{L}} $$ will be to stratify patients into preoperative risk categories after neoadjuvant cancer treatment: low risk $$ \overset{.}{\mathrm{V}}{\mathrm{o}}_2 $$ at $$ {\widehat{\uptheta}}_{\mathrm{L}} $$ >14.1 ml.kg^-1^.min^-1^; medium risk $$ \overset{.}{\mathrm{V}}{\mathrm{o}}_2 $$ at $$ {\widehat{\uptheta}}_{\mathrm{L}} $$ 11.0–14.0 ml.kg^-1^.min^-1^; high-risk $$ \overset{.}{\mathrm{V}}{\mathrm{o}}_2 $$ at $$ {\widehat{\uptheta}}_{\mathrm{L}} $$ 8.1–10.9 ml.kg^-1^.min^-1^; highest risk $$ \overset{.}{\mathrm{V}}{\mathrm{o}}_2 $$ at $$ {\widehat{\uptheta}}_{\mathrm{L}} $$ <8.0 ml.kg^-1^.min^-1^. CPET derived $$ \overset{.}{\mathrm{V}}{\mathrm{o}}_2 $$ peak will be defined as the average $$ \overset{.}{\mathrm{V}}{\mathrm{o}}_2 $$ over the last 30 s of exercise.

#### Postoperative morbidity

Post-operative morbidity will be objectively recorded using POMS at day 3, 5, 7 and 15 days following surgery, in order to explore the relationship between neoadjuvant cancer treatments, surgery and short-term post-operative harm. The POMS [9, 10] is a validated measure of short-term post-operative harm which includes an 18-item tool that addresses nine domains of morbidity relevant to the post-surgical patient: pulmonary, infection, renal, gastrointestinal, cardiovascular, neurological, wound complications, haematological and pain. For each domain either presence or absence of morbidity will be recorded on the basis of precisely defined clinical criteria.

#### Patient reported outcomes measure

Patient Reported Outcomes will be described using EQ-5D-5 L [11], which has been recommended for use as a generic PROM following major surgery. This will be measured at several time points; pre- and post-neoadjuvant cancer treatment, and 30-days and 1-year post-surgery. This questionnaire includes a health scale and also encompasses the following 5 domains; 1) mobility, 2) self-care, 3) usual activities, 4) pain/discomfort 5) anxiety/depression.

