## Background

Worldwide, oesophageal cancer is the eighth most common cancer and the sixth most common cause of cancer death, while gastric cancer is the fifth most common cancer and third most common cause of cancer-death. In England and Wales, approximately 21,200 patients were diagnosed with oesophageal or gastric cancer in 2014, of which 37 % underwent planned curative treatment [1, 2]. Although potentially curative, surgical resection is attempted in up to 80 % of those patients planned for curative treatments, however significant morbidity and mortality is reported. The reported 90-day mortality rates for oesophagectomy and gastrectomy are 4.4 % and 4.3 % respectively, with 1-year survival rates between 76.1 % and 78.0 % depending on the site of the primary tumour [1]. A large updated meta-analysis provides evidence that for operable OG disease neoadjuvant therapies improve survival over surgery alone [3]. In the UK the MAGIC trial has resulted in a practice change in favour of neoadjuvant chemotherapy (NAC) [4]. Treatment with neoadjuvant therapies carries the risk of toxicity and in clinical practice this may be associated with an increased risk of surgical morbidity [3]. Cardiopulmonary exercise testing (CPET) provides an objective assessment of physical fitness through evaluating cardio-respiratory function under the stress of exercise mimicking the stress of major surgery. Variables derived from CPET such as oxygen uptake at estimated lactate threshold ($$ \overset{.}{\mathrm{V}}{\mathrm{o}}_2 $$ at $$ {\widehat{\uptheta}}_{\mathrm{L}} $$) and at peak exercise ($$ \overset{.}{\mathrm{V}}{\mathrm{o}}_2 $$ peak) are associated with worse outcome following UGI surgery [5, 6].

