In a preliminary study, we showed, in a small number of patients, that neoadjuvant chemotherapy (NAC) before upper gastrointestinal (UGI) cancer surgery significantly reduced physical fitness [7]. In this study, lower baseline fitness was associated with reduced 1-year-survival in patients completing NAC and surgery, but not in patients who did not complete NAC. We therefore speculated that in some patients the harms of NAC may outweigh the benefits and set out to test the hypothesis that neo-adjuvant chemotherapy (or chemoradiotherapy) was associated with reduced physical fitness ($$ \overset{.}{\mathrm{V}}{\mathrm{o}}_2 $$ at $$ {\widehat{\uptheta}}_{\mathrm{L}} $$ measured using CPET) and that this fall in $$ \overset{.}{\mathrm{V}}{\mathrm{o}}_2 $$ at $$ {\widehat{\uptheta}}_{\mathrm{L}} $$ would in turn be associated with increased harm (mortality at 1 year) following surgery.

In this manuscript, we describe the design of a prospective, observational, observer blinded cohort study investigating the effects of neoadjuvant cancer therapies (both chemo- and chemoradio-therapy – NAC/CRT) on exercise capacity and clinical outcome in patients undergoing surgery for UGI cancer.

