Primary hypotheses:Neoadjuvant cancer treatment will result in a decrease in physical fitness ($$ \overset{.}{\mathrm{V}}{\mathrm{o}}_2 $$ at $$ {\widehat{\uptheta}}_{\mathrm{L}} $$), measured using CPET.The change in physical fitness ($$ \overset{.}{\mathrm{V}}{\mathrm{o}}_2 $$ at $$ {\widehat{\uptheta}}_{\mathrm{L}} $$) associated with neoadjuvant cancer treatment will be associated with mortality 1 year after surgery. This second hypothesis will be evaluated in two separate ways:A)The relative decrease in physical fitness ($$ \overset{.}{\mathrm{V}}{\mathrm{o}}_2 $$ at $$ {\widehat{\uptheta}}_{\mathrm{L}} $$) associated with neoadjuvant cancer treatment prior to UGI cancer resection will be associated with mortality at 1 year after surgery.Secondary hypotheses:B)Patients whose physical fitness ($$ \overset{.}{\mathrm{V}}{\mathrm{o}}_2 $$ at $$ {\widehat{\uptheta}}_{\mathrm{L}} $$) changes their risk stratification category (low risk $$ \overset{.}{\mathrm{V}}{\mathrm{o}}_2 $$ at $$ {\widehat{\uptheta}}_{\mathrm{L}} $$ >14 ml.kg.^-1^min^-1^, medium risk $$ \overset{.}{\mathrm{V}}{\mathrm{o}}_2 $$ at $$ {\widehat{\uptheta}}_{\mathrm{L}} $$ 11.0–14.0 ml.kg^-1^.min^-1^, high-risk $$ \overset{.}{\mathrm{V}}{\mathrm{o}}_2 $$ at $$ {\widehat{\uptheta}}_{\mathrm{L}} $$ 8.0–10.9 ml.kg^-1^.min^-1^, highest risk $$ \overset{.}{\mathrm{V}}{\mathrm{o}}_2 $$ at $$ {\widehat{\uptheta}}_{\mathrm{L}} $$ <8.0 ml.kg^-1^.min^-1^) following neoadjuvant cancer treatment would have an increased 1-year mortality following surgery when compared with those who do not increase risk stratification category.Pre-NAC variables (including CPET derived variables) can be modelled to predict post NAC $$ \overset{.}{\mathrm{V}}{\mathrm{o}}_2 $$ at $$ {\widehat{\uptheta}}_{\mathrm{L}} $$.Exploratory hypotheses:The relative decrease in physical fitness ($$ \overset{.}{\mathrm{V}}{\mathrm{o}}_2 $$ at $$ {\widehat{\uptheta}}_{\mathrm{L}} $$) associated with neoadjuvant cancer treatment prior to UGI cancer resection will be associated with i) increased post-operative morbidity, assessed using the Post-Operative Morbidity Survey (POMS), and ii) worse patient reported outcome assessed using EQ-5D quality of life questionnaire.The relative decrease in peak oxygen consumption ($$ \overset{.}{\mathrm{V}}{\mathrm{o}}_2 $$ peak) associated with neoadjuvant cancer treatment prior to UGI cancer resection will be associated with i) increased post-operative morbidity, assessed using POMS, ii) worse patient reported outcome, assessed using EQ-5D quality of life questionnaire and iii) decreased 1 year survival.Patients with a lower exercise capacity ($$ \overset{.}{\mathrm{V}}{\mathrm{o}}_2 $$ at $$ {\widehat{\uptheta}}_{\mathrm{L}} $$ and $$ \overset{.}{\mathrm{V}}{\mathrm{o}}_2 $$ peak) tolerate NAC prior to upper gastrointestinal cancer resection (in terms of patient reported outcome and compliance with NAC protocol) less well than patients with a higher exercise capacity.Patients who do not tolerate NAC prior to upper gastrointestinal cancer resection (in terms of PROMS and compliance with NAC protocol) have a worse postoperative outcome (1-year mortality, POMS, EQ-5D).Changes in CPET derived variables will explain mechanisms of NAC associated exercise limitation.CRT (CROSS style chemoradiotherapy) will result in a greater fall in $$ \overset{.}{\mathrm{V}}{\mathrm{o}}_2 $$ at $$ {\widehat{\uptheta}}_{\mathrm{L}} $$ and $$ \overset{.}{\mathrm{V}}{\mathrm{o}}_2 $$ peak between pre- and post- neoadjuvant cancer treatments than NAC (MAGIC type chemotherapy).

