### Data elaboration and statistical analysis

#### Sample size calculation

Hypothesis 1: A sample of 152 patients would be required to detect a difference in 1.0 ml.kg^.-1^.min^-1^ of $$ \overset{.}{\mathrm{V}}{\mathrm{o}}_2 $$ at $$ {\widehat{\uptheta}}_{\mathrm{L}} $$ using a paired t-test at the 5 % significance level with 90 % power. This is assuming the standard deviation of the difference in $$ \overset{.}{\mathrm{V}}{\mathrm{o}}_2 $$ at $$ {\widehat{\uptheta}}_{\mathrm{L}} $$ values is 3.8 ml.kg^.-1^.min^-1^. A smaller sample of 114 patients would provide 80 % power.

Hypothesis 2A: A sample size of 242 is required to detect a difference in 1 year mortality rates of 15 % [30 % versus 15 %] between the two AT change groups [no change/deteriorate] using a chi-squared test at the 5 % significance level with 80 % power, assuming equal numbers of patients in both groups. A smaller sample of 104 patients will be able to detect a difference of 23 % [34 % vs 11 %] with 80 % power.

The aim for hypothesis 2A is to compare the predictive ability of both models to ascertain how prognostic the relative decrease in exercise capacity is, after adjusting for baseline exercise. Approximately 250 patients are required to develop reliable prediction models containing 5 factors [e.g. age, gender, centre, location of tumour, laparoscopic vs. open]. This is using the “Rule of 10” and assumes that the 1-year mortality rate is 20 % [conservative estimate]. Given a 30 % non-completion of NAC and 2 CPET tests based on Liverpool data, approximately 360 patients will need to be recruited. With a smaller sample of 104 patients and 25 % mortality rate, we can develop reliable prediction models (using standard methods) that contain fewer factors, e.g. 3. In addition, we plan to use “penalised” regression models that are able to contain more factors, even when the “Rule of 10” is not met [12].

We therefore set out to recruit 250 patients into this study in 4 centres over 24 months. The volume of eligible patients in these 4 centers is approximately 200 patients per year. We therefore estimate that the study recruitment time would take less than 24 months based on a 66 % recruitment rate (132 patients per year).

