#### Statistical analysis

Descriptive analyses will be carried out to summarise patient characteristics. Continuous variables will be presented as either mean (standard deviation) or median (inter-quartile) as appropriate. The distribution of the continuous variables will be investigated using histograms. Categorical variables will be presented as frequency (%).

The primary analysis will be a comparison of physical fitness ($$ \overset{.}{\mathrm{V}}{\mathrm{o}}_2 $$ at $$ {\widehat{\uptheta}}_{\mathrm{L}} $$) before and after neoadjuvant cancer treatment using a paired t-test. Distributional assumptions will be assessed using a normal plot. If these are not met then Wilcoxon matched-pairs signed-ranks test will be used. Survival at 1 year will be compared between ‘change in fitness’ groups using either the χ2 test (or Fisher’s exact test if cell counts are insufficient) or log-rank test depending on the degree of censoring throughout the year. Either logistic or Cox regression methods will be used to investigate the relationship between fitness and mortality, adjusted for confounders. The calibration and discrimination of these models will be assessed. The relationship between morbidity and fitness will be explored using mixed models that account for the fact that morbidity is measured on several occasions post-surgery.

All estimates will be given with 95 % confidence intervals. Missing data will be investigated though imputation is not planned as we do not expect a large proportion of missing data. All analyses will be performed with the statistical software Stata 14.0.

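### The reason given for no imputation does not fit the 1-year EQ-5D: 20–25 % of patients are expected to have died by then, more of them where fitness fell, so a survivor-only result is likely to understate the association

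*Protocol article*

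**What the plan says.** All places are in the protocol article.

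- **Patient reported outcomes measure** and **Table 1**: EQ-5D is taken "pre- and post-neoadjuvant cancer treatment, and 30-days and 1-year post-surgery".
- **Aims, exploratory hypotheses**: the relative fall in oxygen uptake at lactate threshold is linked to "worse patient reported outcome assessed using EQ-5D quality of life questionnaire". No time point is named there. A later exploratory hypothesis, on patients who do not tolerate neoadjuvant chemotherapy, lists EQ-5D as a postoperative outcome beside 1-year mortality.
- **Aims, primary hypothesis 2A**: the same relative fall in fitness "will be associated with mortality at 1 year after surgery".
- **Background**: the literature is reported "with 1-year survival rates between 76.1 % and 78.0" %, that is, 22.0–23.9 % dead at 1 year. Reported 90-day mortality is 4.3–4.4 %.
- **Sample size calculation**: 1-year mortality is put at 20 % for the prediction models and at 25 % for the smaller sample. The comparison "between the two AT change groups [no change/deteriorate"] uses 30 % v 15 %, or 34 % v 11 % with 104 patients.
- **Statistical analysis**: "imputation is not planned as we do not expect a large proportion of missing data". The section names methods for fitness, 1-year survival and morbidity. It names none for EQ-5D and does not mention deaths in connection with missing data.

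**The concern.** The missing-data sentence covers every outcome and gives a reason. For the 1-year EQ-5D the reason fails on the article's own planning figures: between a fifth and a quarter of patients cannot have a value because they will have died. With no imputation and no mention of death, the analysis that results by default uses survivors only.

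The loss is also not expected to be even. The exposure in the EQ-5D hypothesis is the exposure in hypothesis 2A. If 2A is right, death removes more patients where fitness fell. If those who die would also have had poorer quality of life, the survivors of that group are the more strongly selected, and the EQ-5D contrast shrinks. The study could then describe quality of life at 1 year as similar in patients whose mortality had doubled. That matters because the Discussion and Conclusion want the results to inform patient selection and consent.

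**Working it through.** **1. The plan's own figure.** Hypothesis 2A: 30 % v 15 %, chi-squared test, two-sided 5 %, 80 % power, equal groups, pooled proportion (0.30 + 0.15)/2 = 0.225.

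n per group = [1.960 × √(2 × 0.225 × 0.775) + 0.842 × √(0.30 × 0.70 + 0.15 × 0.85)]² / 0.15² = 120.5, rounded up to 121. The total is 242, as stated. The mortality split used below is therefore the one the plan was sized on.

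**2. How many 1-year values death removes.**

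- Overall: 20–25 %, or about 50–63 per 250 patients who have surgery. Both planning splits average 22.5 %: (30 + 15)/2 and (34 + 11)/2.
- By group at 121 each, 30 % v 15 %: alive 121 × 0.70 ≈ 85 v 121 × 0.85 ≈ 103.
- By group at 52 each, 34 % v 11 %: alive 52 × 0.66 ≈ 34 v 52 × 0.89 ≈ 46.
- The proportion lost is twice as high (30/15) or about three times as high (34/11) in the deteriorating group.
- At 30 days the loss must be small, since even 90-day mortality is only 4.3–4.4 %. The two preoperative assessments lose nothing to postoperative death.

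**3. What survivor selection does to the contrast.** The article gives neither a true EQ-5D effect nor the link between health and death, so both are assumed. Let u be latent health, standard normal. The 1-year EQ-5D a patient would have is 0.75 − 0.04 × (deteriorated) + 0.12u + noise with SD 0.1. Death follows a probit model with loading λ on u, set to give the planned mortality p in each group.

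- Mean of the standardised survival score among survivors: m(p) = φ(z_p)/(1 − p). This gives m(0.30) = 0.497, m(0.15) = 0.274, m(0.34) = 0.555 and m(0.11) = 0.211.
- Its correlation with u: λ/√(1 + λ²), which is 0, 0.447 and 0.707 for λ = 0, 0.5 and 1.0.
- Shift towards zero = 0.12 × correlation × [m(p deteriorated) − m(p no change)].

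| Mortality | λ | Shift | Survivor-only difference (true −0.040) | Share lost |
|---|---|---|---|---|
| 30 % v 15 % | 0 | 0 | −0.040 | 0 % |
| 30 % v 15 % | 0.5 | 0.012 | −0.028 | 30 % |
| 30 % v 15 % | 1.0 | 0.019 | −0.021 | 47 % |
| 34 % v 11 % | 0.5 | 0.018 | −0.022 | 46 % |
| 34 % v 11 % | 1.0 | 0.029 | −0.011 | 73 % |

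In SD units, without assuming an index scale, the shift is ρ × [m(p deteriorated) − m(p no change)], where ρ is the within-group correlation between frailty and 1-year health. For ρ = 0.3, 0.5 and 0.7 it is 0.07, 0.11 and 0.16 SD at 30 % v 15 %, and 0.10, 0.17 and 0.24 SD at 34 % v 11 %. It is zero at ρ = 0.

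**4. What counting death does.** If survivors in both groups averaged an assumed 0.75 and death were scored 0, the difference would be 0.75 × (0.85 − 0.70) = 0.11, while the survivor-only difference would be 0. Under the model in step 3 the death-scored difference at 30 % v 15 % is about −0.13 for λ = 0.5 or 1.0. The two analyses answer different questions.

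**The case against.** **No EQ-5D analysis is written down.** The article states no EQ-5D method, and the two change groups come from the sample-size paragraph; the EQ-5D hypothesis speaks of a relative decrease. How deaths are handled in an exploratory questionnaire is normally left to an analysis plan. This stands, so the absence of a rule for deaths is not the point here. What remains is a stated missing-data reason that does not fit the stated mortality.

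**Imputation is not the remedy.** This also stands. Filling in values for the dead would not answer the question, and the fix does not ask for it.

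**The bias is assumed and small.** No source in the article supports the 0.04 deficit, the variances or the loadings, and with no link between health and death there is no bias. On this model (SD √(0.12² + 0.1²) = 0.156; 85 v 103 survivors) the standard error is 0.156 × √(1/85 + 1/103) = 0.023, larger than the shift of 0.012–0.019. This stands as a limit on the size. It does not remove the direction, which follows if frailer patients both die more and feel worse.

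**Scoring death as 0 has its own distortion.** Mortality alone then produces a quality-of-life difference, as step 4 shows, and mortality is already a primary result. The article describes a health scale and five domains, not an index with a value for death. This stands against making such a score the main analysis, though not against a labelled companion.

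**Stronger readings to avoid.** A reader might infer that all the quality-of-life hypotheses are biased; only the 1-year assessment is materially affected. A reader might infer that fitness loss is hypothesised to cause the deaths; the Background says it "would in turn be associated with increased harm (mortality at 1 year) following surgery". A reader might take the survivors to be exactly the healthiest 70 % and 85 %; that needs death to follow health perfectly, which nothing in the article says.

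**Conclusion.** The point holds for the 1-year EQ-5D only. Expecting little missing data is inconsistent with an expected 1-year mortality of 20–25 %, and on the planning rates the loss is two to three times as high in patients whose fitness fell. A survivor-only analysis is likely, but not certain, to be biased towards no association. The firm part is the proportion lost, which comes from the article. The size of the bias is illustrative: from nothing if health and death are unrelated to about 30–50 % of an assumed 0.04 deficit at 30 % v 15 %, and more at 34 % v 11 %. A survivor-only result remains a valid description of survivors if it is labelled as one. EQ-5D is exploratory in the Aims and Table 1 (the Abstract and the Secondary outcomes heading place it among the secondary ones), and no primary conclusion depends on it. It is a minor point with a cheap remedy.

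**What to change.** In Statistical analysis:

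1. Say that deaths before the 1-year assessment are not treated as ordinary missing data, and confine the expectation of little missing data to patients alive at each time point.
2. Report the 1-year EQ-5D among survivors, labelled as conditional on survival, with the number of deaths by fitness change beside it.
3. Add one companion analysis that counts death, for example death ranked below every observed value, or death set to 0 if an index is derived. Ranking needs no index or value set.

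The cost is a few sentences of analysis wording and an extra row or two in the 1-year table. No new data are needed, because date of death is already obtained for the mortality endpoint. The drawback is that the companion result mixes death with quality of life, so it must be read beside the survivor-only and mortality results and not in place of either. The preoperative and 30-day EQ-5D analyses need no change.

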### Data elaboration and statistical analysis

#### Sample size calculation

Hypothesis 1: A sample of 152 patients would be required to detect a difference in 1.0 ml.kg^.-1^.min^-1^ of $$ \overset{.}{\mathrm{V}}{\mathrm{o}}_2 $$ at $$ {\widehat{\uptheta}}_{\mathrm{L}} $$ using a paired t-test at the 5 % significance level with 90 % power. This is assuming the standard deviation of the difference in $$ \overset{.}{\mathrm{V}}{\mathrm{o}}_2 $$ at $$ {\widehat{\uptheta}}_{\mathrm{L}} $$ values is 3.8 ml.kg^.-1^.min^-1^. A smaller sample of 114 patients would provide 80 % power.

Hypothesis 2A: A sample size of 242 is required to detect a difference in 1 year mortality rates of 15 % [30 % versus 15 %] between the two AT change groups [no change/deteriorate] using a chi-squared test at the 5 % significance level with 80 % power, assuming equal numbers of patients in both groups. A smaller sample of 104 patients will be able to detect a difference of 23 % [34 % vs 11 %] with 80 % power.

The aim for hypothesis 2A is to compare the predictive ability of both models to ascertain how prognostic the relative decrease in exercise capacity is, after adjusting for baseline exercise. Approximately 250 patients are required to develop reliable prediction models containing 5 factors [e.g. age, gender, centre, location of tumour, laparoscopic vs. open]. This is using the “Rule of 10” and assumes that the 1-year mortality rate is 20 % [conservative estimate]. Given a 30 % non-completion of NAC and 2 CPET tests based on Liverpool data, approximately 360 patients will need to be recruited. With a smaller sample of 104 patients and 25 % mortality rate, we can develop reliable prediction models (using standard methods) that contain fewer factors, e.g. 3. In addition, we plan to use “penalised” regression models that are able to contain more factors, even when the “Rule of 10” is not met [12].

We therefore set out to recruit 250 patients into this study in 4 centres over 24 months. The volume of eligible patients in these 4 centers is approximately 200 patients per year. We therefore estimate that the study recruitment time would take less than 24 months based on a 66 % recruitment rate (132 patients per year).

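### The plan's own sum calls for about 360 recruits but the target is 250, leaving about 175 evaluable and 66% power for hypothesis 2A (30% versus 15%) instead of 80%

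*Protocol article*

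**What the plan says.** All the figures are in the protocol article, under Sample size calculation.

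- **Hypothesis 2A, mortality comparison.** "A sample size of 242 is required to detect a difference in 1 year mortality rates of 15" percentage points (30% against 15%), "using a chi-squared test at the 5 % significance level with 80 % power, assuming equal numbers of patients in both groups".
- **Prediction model.** "Approximately 250 patients are required to develop reliable prediction models containing 5 factors", by a rule of ten events per factor that "assumes that the 1-year mortality rate is 20 % [conservative estimate"].
- **Attrition.** "Given a 30 % non-completion of NAC and 2 CPET tests based on Liverpool data, approximately 360 patients will need to be recruited".
- **Reduced scenario.** 104 patients would detect 34% versus 11% with 80% power and, at 25% mortality, support about three factors. Penalised regression is planned for models with more factors than the ten-events rule allows.
- **Target.** "We therefore set out to recruit 250 patients into this study in 4 centres over 24 months". Accrual is put at 132 patients per year, so recruitment is expected to finish in under 24 months.

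**The concern.** The 242 and the 250 are numbers of patients who can be analysed. The exposure in hypothesis 2A is the change in oxygen uptake at lactate threshold between two exercise tests, so a patient without both tests has no exposure value. The Statistical analysis section plans no imputation. The plan recognises this when it inflates 250 to about 360, and then sets the target at 250 as though that followed.

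The abstract, the Aims and the Primary outcome section all give 1-year mortality or its association with fitness change primary status. The Discussion and Conclusion look to the results for selecting patients for neoadjuvant treatment. If the 2A result is null, readers will judge it against 80% power for a 15-point difference, which the recruitment target does not provide. A five-factor model would also be taken as adequately supported when, by the plan's own rule, it is not.

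**Working it through.** **Inputs, all from Sample size calculation:** mortality 30% and 15%; 5% significance (two-sided assumed); equal groups; 80% power; 250 patients for five factors at 20% mortality; 30% non-completion; 132 recruits per year; for hypothesis 1, difference 1.0 and SD of differences 3.8 ml/kg/min.

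**1. Reproduce the plan's figures.**
- Chi-squared comparison, with pooled variance under the null and no continuity correction: n per group = [1.96·√(2·0.225·0.775) + 0.842·√(0.30·0.70 + 0.15·0.85)]² / 0.15² = (1.157 + 0.489)² / 0.0225 ≈ 120.5, rounded up to 121. The total is 242, as stated.
- Model: 250 × 0.20 / 10 = 5 factors, as stated.
- Attrition: 250 / 0.70 = 357, given as about 360.

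**2. Is 250 recruited or evaluable?** 250 / 132 × 12 = 22.7 months, which matches the stated period of under 24 months. Recruiting 360 would take 360 / 132 × 12 = 32.7 months. So 250 is the number recruited.

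**3. Evaluable patients.** 250 × 0.70 = 175, or 87.5 per group.

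**4. Power for hypothesis 2A at 175.** z = (0.15·√87.5 − 1.157) / 0.581 = (1.403 − 1.157) / 0.581 = 0.423, so power is Φ(0.423) = 66.4%. The same formula gives 80.2% at 242.

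**5. Difference detectable with 80% power at 175.** About 33% versus 15% (18.0 points), or 17.6 points if centred on 22.5%.

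**6. Sensitivity of the 2A power to non-completion, with 250 recruited.**

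| Non-completion | Evaluable | Power, 30% vs 15% |
|---|---|---|
| 10% | 225 | 77% |
| 20% | 200 | 72% |
| 30% | 175 | 66% |
| 40% | 150 | 60% |

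With change groups split 2:1 instead of equally, power at 175 is 59% to 64%, depending on which group is larger.

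**7. Model size at 175.** At 20% mortality: 175 × 0.20 = 35 deaths, 3.5 factors. At 25% (the rate in the reduced scenario): 43.75 deaths, 4.4 factors. The 1-year survival of 76.1% to 78.0% quoted in the Background implies mortality of 22.0% to 23.9%, hence 38.5 to 41.8 deaths and 3.9 to 4.2 factors. None of these reaches five.

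**8. What 175 does support.** Hypothesis 1: 175 pairs give 93% power by paired t-test. The reduced scenario of 34% versus 11% has 96% power.

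**The case against.** The strongest defence is that 250 was a deliberate compromise. The 104-patient scenario and the penalised models are described immediately before the target is set, and the plan never says in one sentence that 250 recruits give 80% power for 15 points. At 175 evaluable the reduced scenario is comfortably covered, and penalised regression is named for exactly the case where events fall short of the rule. This stands in part, and a restatement should cite both. But the plan does not say that it moved to the reduced scenario, and 250 does not come from it: 104 / 0.70 is about 149. That scenario concerns a 23-point difference, and penalised regression does nothing for the chi-squared comparison.

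Second, mortality's status is not uniform. Table 1 lists only physical fitness as primary and places survival under the exploratory endpoints, and Statistical analysis names the paired t-test as the primary analysis. That is true, and hypothesis 1 is safe. The abstract, the Aims and the Primary outcome section still treat mortality as primary, so its power statement has to be right.

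Third, 66% is the power of an unadjusted two-group test, while the plan also foresees logistic or Cox models and possibly a log-rank test. This is a fair limit on what the figure means. It is, however, the test on which the plan itself sized hypothesis 2A.

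Finally, the individual sums in the section are all correct. The fault lies in the step from 360 to 250, which is not explained.

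**Conclusion.** The concern holds. The recruitment target contradicts the plan's own attrition calculation by about 110 patients (360 − 250). Taken at its word, the design yields about 175 evaluable patients, 66% power for 30% versus 15% where the section gives 80%, and about 35 deaths where five factors need 50. The chance of missing the planned mortality difference rises from 20% to about 34%.

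This rests on the plan's 30% non-completion and equal groups, on a two-sided test (which reproduces 242 exactly), and on non-completers contributing nothing to the change-in-fitness analysis. The conclusion does not depend on the exact 30%: at 10% non-completion, power is still below 80%. The expectation in Statistical analysis that little data will be missing sits badly with a 30% non-completion rate and does not help. Hypothesis 1 is unaffected.

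**What to change.** Rewrite the end of the Sample size calculation so that target and justification agree:

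- State 250 recruited and, after 30% non-completion, about 175 evaluable. Label every sample size in the section as recruited or evaluable.
- Hypothesis 1: 93% power for a 1.0 ml/kg/min difference with SD 3.8.
- Hypothesis 2A: 66% power for 30% versus 15%; 80% power for about 18 points (33% versus 15%); 96% power for the 34% versus 11% scenario already in the text.
- Prediction model: about 35 deaths at 20% mortality, supporting three factors under the ten-events rule (about 44 deaths and four factors at 25%), with penalised regression named as the approach for anything larger. Keep the plan's word, factors: centre has four sites and would use three parameters if entered as categories.
- Say explicitly that the figure of about 360 was not adopted, and why.

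The cost is a few sentences of redrafting and a less favourable power statement for hypothesis 2A. No additional patients or changes to study conduct are needed.
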